## Methods

### Study design

A cluster randomized controlled trial will be carried out on breastfeeding mothers referred to health centers affiliated to Tehran University of Medical Sciences. A cluster randomized controlled trial design was chosen because it makes it easier for mothers to attend classes at their local health center, and in this design, the phenomenon of contamination between the intervention and control groups is avoided. Besides, it can help us increase the representativeness and generalizability of our study population and results. The control group allows us to analyze the direct effect of the intervention and discount an increase in milk donation due to other factors [20]. This study was approved by the Research Ethics Committees of School of Nursing and Midwifery & Rehabilitation - Tehran University of Medical Sciences (IR.TUMS.FNM.REC.1401.150).

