### Setting

This study will be conducted in health centers affiliated to Tehran University of Medical Sciences. Tehran University of Medical Sciences covers primary health care services of 5 out of 22 districts of Tehran City (district numbers 10, 11, 16, 17 and 19) [21]. These health centers were chosen because they cover a significant portion of breastfeeding mothers of South Tehran, who usually bring their infants to theses\ health centers for vaccination, screening or growth monitoring. However, we will include four of these districts in our study (district numbers 10, 11, 16 and 17) because the health centers of district number 19 do not have the equipment for holding in-person classes and the population of Iranian breastfeeding mothers in that district is limited. These four districts have a total of 20 health centers. From among all these health centers, we will choose eight centers using simple randomization method; then, a cluster of four centers will be randomly selected for collecting the intervention group and four centers for collecting the control group. We will recruit eight to nine participants from each health center.

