### Sample size

In order to provide a power of 95% with 95% confidence interval the following formula and the standard deviation of 3.17 to 3.21 (according to the same study’s findings) will be used [18]. The sample size was estimated at 30, and then allowing for 10% attrition, we plan to recruit 33 samples per group and a total of 66 study participants.$$ n=\frac{{\left({z}_{1-\frac{\alpha }{2}}+{z}_{1-\beta }\right)}^{2}\left({s}_{1}^{2}+{s}_{2}^{2}\right)}{{\left({\overline{x}}_{1}-{\overline{x}}_{2}\right)}^{2}}$$$$ \frac{{\left(1.96+1.64\right)}^{2}\left({3.21}^{2}+{3.17}^{2}\right)}{{3}^{2}}=29.4\cong 30$$$$ 30+30\left(0.1\right)=33$$

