### Statistical analysis

We will use descriptive analysis to report baseline characteristics. In this study the Repeated ANOVA between subjects test will be used for quantitative variables which have a normal distribution, and the Friedman test will be used for quantitative variables that do not have a normal distribution. For qualitative variables, chi-square test or Fisher’s exact test will be used. The effectiveness of the intervention will be assessed using the repeated measure ANOVA test and the effect of demographic variables on milk donation behavior will be determined using a logistic regression model. Statistical analyses will be made using IBM-SPSS 22. The trial has been registered at the Iranian Registry of Clinical Trials (IRCT20230124057203N1).

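### Health centers are randomised, but the tests named for effectiveness treat mothers as independent, so type I error can exceed 5% and intervals are too narrow if outcomes correlate within centers

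*Protocol article*

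**What the plan says.** The Study design section fixes the unit of allocation: "A cluster randomized controlled trial will be carried out on breastfeeding mothers referred to health centers". The Setting section gives the numbers. Eight of 20 centers are drawn at random, and then "a cluster of four centers will be randomly selected for collecting the intervention group and four centers for collecting the control group". It adds: "We will recruit eight to nine participants from each health center". The Intervention design section has the sessions held in the intervention centers, with small-group discussion and role-play.

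The Statistical analysis section states: "The effectiveness of the intervention will be assessed using the repeated measure ANOVA test". It names a between-subjects repeated-measures ANOVA for normally distributed quantitative variables, the Friedman test for the others, and chi-square or Fisher's exact test for qualitative variables, which include donated yes/no. Logistic regression is named for the effect of demographic variables on donation. The article mentions no center term, mixed model, center-level analysis, ICC or design effect.

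The primary outcomes (Data collection section) are the number of donors and the changes in knowledge, attitude, norms, perceived control and intention.

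**The concern.** When centers are allocated, the arms differ by the program and also by which four centers each arm received. A mother-level test judges the difference only against variation between mothers, as if there were 66 independent units (66 - 2 = 64 degrees of freedom). Eight centers give 8 - 2 = 6.

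The article itself makes a positive correlation plausible. Centers come from four districts, mothers are taught together, and clustering is justified partly by the risk of contamination, which assumes that mothers at the same center influence one another. Both kinds of primary outcome are affected. A significant result could then reflect which centers were drawn rather than the program.

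**Working it through.** **Inputs from the article.** Eight centers, four per arm. 33 mothers per arm, so 33/4 = 8.25 per center (8, 8, 8, 9 in the simulations). Two-sided alpha 0.05, power 95%, SDs 3.21 and 3.17, difference 3 (Sample size section).

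**Assumed, because the article gives no figure.** ICC 0.01 to 0.20; donor proportion 10% to 40%; within-mother correlation 0.5 over the three assessments.

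**Step 1: the plan's own figure.** (1.96 + 1.64)² × (3.21² + 3.17²) / 3² = 12.96 × 20.353 / 9 = 29.31 (29.39 with unrounded z values), hence 30. Then 30 × 1.1 = 33. The stated size reproduces, but only with the formula for independent individuals. Sizing and analysis share the same omission.

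**Step 2: one comparison of mother-level means.** Design effect DE = 1 + (8.25 - 1) × ICC. Approximate true type I error = 2 × [1 - Φ(1.96/√DE)]. A valid 95% interval on 6 df is √DE × 2.447/1.998 times the unadjusted width.

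| ICC | DE | Type I error, formula | Simulated | Valid / unadjusted width |
|---|---|---|---|---|
| 0.01 | 1.07 | 5.8% | about 6% | 1.27 |
| 0.05 | 1.36 | 9.3% | 9-10% | 1.43 |
| 0.10 | 1.73 | 13.6% | 14% | 1.61 |
| 0.20 | 2.45 | 21% | 22% | 1.92 |

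A t-test on center means (6 df) held 5% in the same simulations.

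**Step 3: the ANOVA that is named.** The section does not say which term is the effectiveness test, so both matter.
- *Between-subjects effect.* This compares each mother's average over three assessments. With within-mother correlation 0.5 its variance is 0.5 + 0.5/3 = 0.667 of a single score, so the ICC of the average is ICC/0.667 = 1.5 × ICC. At ICC 0.05, DE = 1 + 7.25 × 0.075 = 1.54 and the formula gives 11.5%. Simulation gives about 6%, 11-12%, 17-18% and 28-29% at the four ICCs.
- *Group-by-time.* Center differences that are constant over time cancel, and simulated type I error stays at about 5%. If centers also differ in change over time, it is about 8%, 11%, 18% and 30% when the center-by-time component is 0.02, 0.05, 0.10 and 0.20 of the within-mother variance.

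**Step 4: donation yes/no** (beta-binomial simulation, uncorrected chi-square).

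| ICC | Chi-square, 10-40% donors | Fisher, 10% donors | Fisher, 20-40% donors |
|---|---|---|---|
| 0.01 | 6-7% | 1.4% | 3-4% |
| 0.05 | 10-11% | 3% | 5-7% |
| 0.10 | 14-16% | 5% | 8-11% |
| 0.20 | 21-24% | 10% | 15-18% |

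**Step 5: power of a valid analysis.** SE = 3.19 × √(2 × DE/33), where 3.19 is the pooled SD; noncentral t on 6 df with noncentrality 3/SE. At ICC 0, SE = 0.785, noncentrality is 3.82 and power is 89%. At ICC 0.01, 0.05, 0.10 and 0.20 power is 86%, 78%, 68% and 53%. If 30 per arm complete (7.5 per center), it is 86% at ICC 0 and about 75% at ICC 0.05.

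**The case against.** The best defence is that an article condenses the plan and that clustering is handled in an analysis plan not shown. That would excuse silence. It does not excuse naming specific tests that do not fit the allocation, and the sample size calculation makes the same independence assumption.

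Three other objections do stand.
- A reader might infer that the false-positive rate exceeds 5% for every outcome. The documents do not support this. They give no ICC, and near 0.01 the inflation is slight. Fisher's exact test is conservative. At 10% donors the expected count is 3.3 donors per arm, where Fisher would normally be chosen, and its error stays at or below about 5% up to ICC 0.10.
- The group-by-time test is not inflated by stable center differences. It needs centers to differ in change over time. Teaching mothers in groups can cause that, but it is not certain.
- A reader might count logistic regression among the effectiveness tests. The article assigns it to demographic effects only. The Friedman test also ignores center, but it tests change within mothers rather than a difference between arms, which is a separate matter.

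The t-test figures in Step 2 are illustrative, since the article does not name that test for effectiveness.

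**Conclusion.** The concern holds in conditional form. The stated effectiveness analysis ignores the randomised unit for both kinds of primary outcome. Given a positive ICC, confidence intervals are too narrow and type I error can exceed 5%. Over ICC 0.01 to 0.20 it is about 6% to 22% for a simple mother-level comparison, 6% to 29% for the ANOVA between-subjects effect, and 6% to 24% for uncorrected chi-square. Fisher's exact test on rare donation, and group-by-time with stable center effects, can remain near or below 5%. These sizes rest on the assumed ICC, donor proportion and within-mother correlation. The mismatch between allocation and analysis does not depend on them. With eight centers, the few degrees of freedom matter even at ICC 0, where a valid interval is 2.447/1.998 = 1.22 times as wide. This should be corrected before analysis.

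**What to change.** Amend the Statistical analysis section as follows.
- **Scores:** compare baseline-adjusted center means by a t-test on 6 df. Alternatively, use a linear mixed model with random intercepts for center and mother and small-sample degrees of freedom, adding a random center-by-time term if group-by-time is the test. State which term is the effectiveness test.
- **Donation:** compare center-level proportions by a t-test on 6 df, or by an exact permutation test over the C(8,4) = 70 possible allocations. The smallest two-sided p-value is 2/70 = 0.029, so significance at 5% remains attainable.
- **Robust standard errors:** do not rely on uncorrected sandwich errors with eight centers.
- **Reporting:** give the estimated ICC for each primary outcome.
- **Logistic model for demographic effects, if kept:** enter center as a random effect. Centers are nested in arm, so fixed center effects would leave any arm effect unidentifiable.

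The data collected do not change, and SPSS can fit the mixed model. The cost is wider intervals and power below the stated 95%: 89% at ICC 0, then 86%, 78%, 68% and 53% at ICC 0.01, 0.05, 0.10 and 0.20 with 33 per arm. The Sample size section should therefore restate power with an explicit ICC, which may reopen the number of centers.

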### Objectives

The main objective of this study is to assess the effectiveness of an educational intervention based on TPB in breastfeeding mothers on donating breast milk to HMBs.

Secondary objectives of the study are:

To evaluate changes in breastfeeding mothers’ knowledge about milk donation.To evaluate the effect of the educational program on behavioral determinants (attitude, subjective norms, perceived behavioral control and behavioral intention).To analyze the association of behavioral determinants with milk donation.To study the relationship between social demographic variables and milk donation.

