### Development of the measurement tool

Data will be measured by a 46-item researcher-made questionnaire. This instrument has been created by reviewing literature on milk donation and previous studies on TPB and consists of seven sections as described in Table 2.

**Table 2 Tab2:** Theory of planned behavior-based survey questions

Sections	Example of questions	Scale
Sociodemographic and perinatal characteristics	Age, education, milk and blood donation history, breastfeeding history, economic status, parity, mode of delivery, the gestational age, sex and age of infant, awareness of HMBs and the source of information of HMBs	-
Knowledge of DHM and HMBs	“What is a human milk bank?” “What is the best alternative to mothers’ own milk for feeding premature babies?” “What effects does pasteurization have on donor milk?” “In the hospital, which babies receive donor milk?” “Who is eligible to donate their breast milk?” “How is donor milk stored in the hospital?” “How long can donated breast milk be stored in the hospital?” “What effects has pasteurized donor milk on premature babies?” “What should mothers do before donating their breast milk?” “What are the characteristics of informal breast milk sharing in the community?”	Multiple-choice questions
Attitude toward DHM and HMBs	“It is pleasant for me to donate breast milk” “Feeding premature babies with donor milk is better than formula” “Donor milk can reduce the stress of mothers who can’t feed their babies with their own breast milk” “By donating breast milk to a milk bank, I can save a baby’s life” “Donating breast milk to the milk bank can reduce the incidence of serious gastrointestinal disease in infants” “Donor milk in milk banks is safe and healthy” “When I don’t have enough breast milk, it is better to use donor milk instead of formula to feed my baby” “Donor milk in a milk bank may carry viruses and spread disease” “Donor milk should be used widely in hospitalized infants who cannot be breastfed, if it is possible” “Donor milk can treat newborns who weigh less than normal” “I think mothers should be rewarded for donating their milk” “After pasteurization, the nutrients in milk are all destroyed, so it is better to feed baby with formula”	5-point Likert (from strongly agree to strongly disagree)

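### An ordinary logistic regression of donation on demographic variables in 66 mothers may have no finite estimates if donors are few; a penalised model with study arm and two or three named covariates would be a cheap improvement to this secondary analysis

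*Protocol article*

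**What the plan says.** One secondary objective is "To study the relationship between social demographic variables and milk donation". The Data collection section repeats these associations as a secondary outcome. The method, in the Statistical analysis section, is that "the effect of demographic variables on milk donation behavior will be determined using a logistic regression model", with SPSS 22 as the software.

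The section names no covariates, does not say whether they enter singly or together, and mentions no method for sparse data. Study arm is not among the variables it names for this model.

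The pool of candidates is the first row of Table 2: "Age, education, milk and blood donation history, breastfeeding history, economic status, parity, mode of delivery, the gestational age, sex and age of infant", followed by awareness of milk banks and the source of that information. Counting milk and blood donation history separately, that makes 11 + 2 = 13 items. The row covers sociodemographic and perinatal characteristics together.

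On size, "The sample size was estimated at 30" per group, and after the attrition allowance "we plan to recruit 33 samples per group and a total of 66 study participants". The calculation uses "the standard deviation of 3.17 to 3.21" and a 3-point difference in means. Donation plays no part in it.

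**The concern.** The information in a logistic model comes from the smaller outcome group, here probably the donors, and not from the number of mothers. When a combination of covariates divides donors from non-donors completely or nearly so, the maximum-likelihood estimate does not exist. Standard software then stops with a warning or prints enormous odds ratios with meaningless standard errors. Separately, if many covariates are tested in one model, some will look significant by chance.

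A third point is study arm. The Hypothesis section expects the intervention to raise donation. Only eight centres are randomised, four per arm, and mothers within them are recruited by convenience, so arms may differ in education or economic status by chance. In a model without arm, an intervention effect could then appear as a demographic one.

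At stake is the answer to one secondary objective. The comparison of the two arms does not depend on this model.

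**Working it through.** **1. The plan's own figure.** (1.96 + 1.64)² × (3.21² + 3.17²) / 3² = 29.3, rounded up to 30 per group; 30 + 30 × 0.1 = 33 per group, 66 in all. The article prints 29.4, which rounds to the same 30. The plan's size is reproduced, but it is a size for a score difference.

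**2. Bound on events per variable (EPV).** EPV = size of the smaller outcome group / number of covariates. With 66 mothers the smaller group is at most 33, so 13 covariates give at most 33/13 = 2.5, whatever the donation rate. With 60 mothers, 3, 10, 20 and 30 donors give 3/13 = 0.23, 10/13 = 0.77, 20/13 = 1.5 and 30/13 = 2.3.

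**3. Simulation with 13 or 4 covariates.** Assumptions: 60 mothers, no true association, independent covariates (about half binary, prevalence 10–50%), 400 datasets per setting. Separation was detected by linear programming. A false predictor means at least one Wald p < 0.05 among fits with finite estimates. The donor counts are assumed.

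| Donors of 60 | Separation, 13 covariates | False predictor, 13 covariates | Separation, 4 covariates | False predictor, 4 covariates |
|---|---|---|---|---|
| 3 | 100% | – | 49% | 3% |
| 5 | 92% | 0% | 13% | 7% |
| 7 | 67% | 21% | 2% | 8% |
| 10 | 44% | 44% | 0.3% | 12% |
| 20 | 14% | 57% | 0% | 20% |
| 30 | 9% | 56% | 0% | 21% |

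With 66 mothers and 13 covariates, separation is similar: 89% with 5 donors and 48% with 10.

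**4. Two different failures.** Separation dominates with few donors, where Wald tests flag almost nothing. False predictors appear from about 7 to 10 donors. They mainly reflect the number of tests: the error per covariate is only about 5–8% from 10 donors up, and 13 independent tests at 5% already give 1 − 0.95¹³ = 49%.

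**5. The narrowest reading.** Suppose only age, education and economic status enter. With three levels each for the last two (an assumption, since the article gives no categories), the model has 1 + 2 + 2 = 5 coefficients. With 60 mothers and no true effect, separation occurred in about 72% of datasets with 5 donors, 44% with 7, 25% with 10 and 7% with 15.

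These figures depend on how evenly the levels are filled. In a further run of 1,000 datasets per setting, a 30/50/20% split of both factors gave 75%, 47%, 26% and 9%. Equal thirds gave 63%, 33%, 10% and 1%. With 20 donors the two splits gave 2% and 0%.

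**The case against.** The strongest reply is that the model with 13 covariates is not in the text. The article speaks of demographic variables, while the Table 2 row also holds mode of delivery, gestational age, infant sex and awareness of milk banks. Nothing says that all items enter together, and a covariate list may properly be left to a fuller analysis plan. This stands: a reader might infer that separation and overfitting follow from the plan as written, and the document does not support that. The 13-covariate figures are conditional on joint entry. The reply does not remove the problem, however, because the narrowest reading still separates often with 5 to 10 donors.

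A reader might also take it as given that donors will be very few. The article states no expected rate. Its Background reports 81 donors in 2020 and 51 in 2021, the latter at one milk bank, but without denominators and not after teaching. Low numbers are plausible, but they remain an assumption.

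Third, one might infer from the Discussion that spurious demographic predictors would shape future programmes. That sentence concerns components of the theory of planned behavior, so this consequence should not be claimed.

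Finally, whether arm enters may also be a detail held elsewhere. It is raised here because the model as described names demographic variables only, and because a change of method is proposed in any case.

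**Conclusion.** The point holds as a cheap improvement to a secondary analysis. With 66 mothers, an ordinary logistic model on the full Table 2 list is not supportable at any donation rate (EPV at most 2.5). Separation or at least one false predictor occurs in 59% to 100% of datasets at the donor counts tabulated above. For example, with 10 donors it is 0.443 + 0.557 × 0.441 = 69%.

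On the narrowest reading the risk depends on the donor count. Separation is about 72% with 5 donors and 25% with 10, and it is rare from about 15 to 20. The 10-donor figure ranges from 10% to 26% across the two level splits that were tried.

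The conclusion rests on assumed donor counts, assumed category levels, independent covariates and no true effect. Steps 3 and 4 use no multi-category items; coding education or information source as several indicators would probably raise separation there.

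**What to change.** In the Statistical analysis section, replace the ordinary model with a Firth-penalised (or exact) logistic model that contains study arm and at most two or three named baseline covariates, for example education and infant age. The penalised fit gives finite estimates even if, say, no control mother donates. Report the remaining Table 2 items descriptively by donor status. Label the analysis exploratory, give confidence intervals, and do not select variables by p-value.

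Prior milk donation should not be a covariate unless the outcome is limited to donations after baseline. The outcome item looks back six months (about 26 weeks), whereas the last assessment falls about 4 + 12 = 16 weeks after baseline. The window therefore reaches some 10 weeks before baseline, and covariate and outcome could count the same donation.

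Arm serves here as an adjustment. Its coefficient should not be read as the test of the intervention.

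Cost: a change of wording, with no change to recruitment or data collection. Fewer variables are modelled, and software other than the planned package may be needed for the penalised or exact fit.

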## Discussion

A well-designed educational program is crucial to improving breastfeeding mothers’ knowledge and behavior regarding milk donation. Especially in Iran, some Muslim mothers may potentially avoid using DHM or donating their breastmilk because they may wrongly assume that milk donation can lead to milk kinship between infants or is not allowed in Islam. However,milk donation is definitely allowed and is even praised as a virtue in Islam, so they need to be informed about Islam Sharia law related to milk donation [17]. In addition, Iranian mothers have a positive attitude towards breastfeeding and the prevalence of exclusive breastfeeding among them is at a satisfactory level [27, 28]. Therefore, educating mothers can lead to a significant increase in the number of potential milk donors [27].

Upon the completion of this study, an increase in milk donation and TPB components scores may indicate that this educational intervention is useful in increasing milk donation behavior. Similarly, negative results can help us devise new strategies in order to improve milk donation behavior. Additionally, in this study we will assess which components of TPB are the most important ones in milk donation behavior, and these findings can guide the content used in future programs and studies.

